### Sample size

2.6

Eighty participants will be enrolled in the study: 40 in experimental group and 40 in control group.

In principle, the sample size in Bayesian designs do not need to be formally justified. Nonetheless, for information and for equivalence with a frequentist design, the following calculation was performed. An a priori distribution was estimated from the elicitation of expert opinions in a pilot study. To limit allegiance bias (associated with the experts' theoretical or treatment preferences), experts were asked to estimate the effect of the care as pessimistically as possible. The following distribution was found for estimates of the difference in the percentage of remission in the two randomized groups: 10%–0%: 0; 0%–10%: 1 expert; 10%–20%: 12 experts; 20%–30%: 4 experts; 30%–40%: 3 experts; 40%–50%: 0. The mean (±SD) of this distribution is 0.195 (±0.0825) and corresponds an a priori of 23 “virtual” subjects per group (the standard deviation 0.0825 being equal to sqrt(*p*[1−*p*]/*n*) where *p* = 0.195 and *n* is the number of virtual subjects per group; Spiegelhalter, Abrams, & Myles, 2004). Added to the 40 “real” subjects (included in this study), the a posteriori overall sample size will therefore be 63 subjects per group. In a frequentist design, a sample size of 63 per group would be sufficient to show a significant 23% difference in efficacy between groups (power = 80%, *α* = 0.05). As TCP is already used for a long time in practice in several centers, the Bayesian design is preferable for ethical reasons (less patients to include), for economical ones and for feasibility (centers could be reluctant to include too many patients).

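### The 23 virtual subjects per group come from a one-proportion standard error applied to a difference between two proportions, so 63 per group and its 80% power do not describe this design

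*Protocol article*

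**What the plan says.** All of this is in the protocol article, section Sample size.

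- Recruitment: "Eighty participants will be enrolled in the study: 40 in experimental group and 40 in control group".
- The prior concerns "estimates of the difference in the percentage of remission in the two randomized groups". The elicited counts are "0%–10%: 1 expert; 10%–20%: 12 experts; 20%–30%: 4 experts; 30%–40%: 3 experts", and "The mean (±SD) of this distribution is 0.195 (±0.0825").
- This is said to be a prior that "corresponds an a priori of 23 “virtual” subjects per group", with "the standard deviation 0.0825 being equal to" the square root of p(1−p)/n at p = 0.195.
- Adding 23 to 40, "the a posteriori overall sample size will therefore be 63 subjects per group".
- On the frequentist side, "a sample size of 63 per group would be sufficient to show a significant 23% difference in efficacy between groups", with power 80% and alpha 0.05.

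No control-group remission rate is given. The section presents the calculation as informative, on the ground that a Bayesian design needs no formal sample size justification. The Primary objective section plans three analyses on the log odds ratio: with the elicited prior, with a pessimistic prior (mean halved, same variance), and with an uninformative prior.

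**The concern.** The values 0.195 and 0.0825 are the mean and SD of a difference between two remission rates. The formula used to turn them into subjects is the standard error of one observed proportion of 19.5%. A difference between two arms of n subjects carries sampling variance from both arms, so an SD of 0.0825 normally takes more subjects per arm than the one-proportion formula gives.

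Two things are at stake. Readers are told, in effect, that the prior counts for 23 against 40 real participants per arm, so that the data dominate. They are also told that the design matches a 63-per-group frequentist trial with 80% power. This is the only numerical support offered for the sample size.

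**Working it through.** **1. The article's own figures.** Bin midpoints 0.05, 0.15, 0.25 and 0.35, weighted 1, 12, 4 and 3, give a mean of 0.195 and a sample SD of 0.0826. Then n = p(1−p)/SD² = 0.195 × 0.805 / 0.0825² = 0.156975 / 0.00680625 = 23.06, and 23 + 40 = 63. The arithmetic reproduces, so the fault lies in the formula.

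**2. The frequentist step.** With the usual two-sided formula (pooled variance under the null) and pC = 0.20, pT = 0.43, mean rate 0.315:

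n = [1.96 × √(2 × 0.315 × 0.685) + 0.842 × √(0.20 × 0.80 + 0.43 × 0.57)]² / 0.23² = 62.8, that is 63 per group, with power 0.801.

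A control rate of 57% gives the same 63. With continuity correction the matches are about 13% and 64%. So 63 per group for 23 points at 80% power is valid arithmetic at one of these unstated rates.

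**3. The two steps do not fit together.** The variance of a difference with n per group is [pC(1−pC) + pT(1−pT)]/n. It equals 0.195 × 0.805/n only if one arm has 0% or 100% remission (0% against 19.5%, or 80.5% against 100%). At 0% control, 23 points would need only 29 per group (38 with continuity correction), not 63. No single control rate supports both the 23 and the 63.

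**4. Corrected virtual number.** n = [pC(1−pC) + pT(1−pT)]/0.0825², with pT = pC + 0.195. The control rate is an assumption, so a range is shown.

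| Control rate | Numerator | Virtual n per group | n + 40 | Prior share n/(n + 40) |
|---|---|---|---|---|
| 5% | 0.2325 | 34 | 74 | 46% |
| 10% | 0.2980 | 44 | 84 | 52% |
| 20% | 0.3990 | 59 | 99 | 59% |
| 30% | 0.4600 | 68 | 108 | 63% |
| 40% | 0.4810 | 71 | 111 | 64% |
| 57% | 0.4249 | 62 | 102 | 61% |
| 70% | 0.3040 | 45 | 85 | 53% |
| 80% | 0.1650 | 24 | 64 | 38% |

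The share implied by the article is 23/63 = 37%.

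**5. Direction of the error.** On the article's additive logic the correction raises the effective size. At 20% control it is about 99 per group, which would give about 94% power for 23 points.

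**6. Virtual subjects are not recruits.** They sit at a 19.5-point benefit whatever the truth is. The elicited prior alone has a 95% interval of 0.195 ± 1.96 × 0.0825, or 0.033 to 0.357, which excludes zero before anyone is enrolled. Adding such subjects to 40 does not give frequentist power with either formula.

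As an illustration, I enumerated all binomial outcomes at 40 per group with a normal prior on the risk difference, counting success as a 95% interval wholly above 0. Scale and success rule are assumptions.

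| Control rates 20% to 40% | Elicited prior | Pessimistic prior | Data alone |
|---|---|---|---|
| Power at a true 23 points | about 98% | 66–74% | 57–62% |

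With no true effect, the elicited-prior interval lies above 0 in about 35% to 45% of trials.

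**The case against.** The best defence is that nothing downstream uses 23 or 63. The Primary objective section weights prior and data by their variances, so correcting the virtual number changes no estimate, interval or decision. The calculation is labelled as informative, and the section also rests the sample size on ethics, economy and feasibility. The three planned analyses already expose the prior's influence, and the Discussion names expert opinion as a limitation. All of this stands and lowers the seriousness. It does not rescue the figures, which are published as the prior's weight and the design's equivalent power. The pessimistic prior also keeps the same variance, so only the uninformative analysis is free of that weight.

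Three stronger readings are tempting, and the document does not support them.

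- *The trial is smaller than claimed.* On the article's own logic the corrected effective size is larger.
- *Expert opinion certainly outweighs the participants.* That depends on an unstated control rate; at 5% or 80% the prior's share is below half.
- *The true power is 98%, 66–74% or 57–62%.* The article states no numerical success rule and analyses the log odds ratio, so these figures only illustrate.

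**Conclusion.** The point holds and should be fixed, though it does not touch the planned analysis. The figure of 23 virtual subjects per group, and with it 63, results from the wrong variance. For control remission of 10% to 70% the elicited SD is worth 1.9 to 3.1 times as many subjects as stated, including 59 at 20% and 62 at 57%, the two rates that reproduce 63 per group without continuity correction. Over that range opinion supplies more than half of the information while the text implies about a third. The 80% power belongs to a conventional trial of 63 real subjects per group at a suitable control rate; it is not a property of 40 per group combined with this prior. The virtual numbers rest on the risk-difference scale that the Sample size section itself uses and on an assumed control rate.

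**What to change.** Keep 80 participants. In the Sample size section:

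1. State the assumed control remission rate.
2. Recompute the virtual number as [pC(1−pC) + pT(1−pT)]/SD².
3. State the prior's resulting share of the information.
4. Withdraw the 63-per-group, 80% power statement as a description of this trial.
5. Give instead the power of 40 per group under each of the three planned priors, naming the scale and the success rule.

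The cost is one rewritten paragraph and a short calculation. No further participants are needed.

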### Randomization

2.3

Participants are randomized with a 1:1 allocation ratio to “usual care and waiting list for TCP for at least 34 weeks” (control group) or “usual care and TCP beginning in the 6 following weeks” (experimental group). Every participant continues his/her usual treatment with the first‐line medical team throughout the duration of the study. As it is a pragmatic real‐life study, usual treatment may vary from one patient to another and from one first‐line medical team to another. It may include psychotherapy (individual, in group, or family therapy), medications, or institutional care (day‐hospital or inpatient care).

The randomization is centralized, stratified according to the recruitment center, with an unknown block size except from the statistician of the research center unit who generated this allocation sequence independently from the investigators and the statistician of the study. The allocation sequence was prepared using NQuery Advisor^®^ v7.0, validated software using pseudorandom numbers generator, and the randomization is performed electronically (IWRS) using the Cleanweb application (Télémédecine) software.

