#### Primary objective

3.1.1

A Bayesian design following the work of Spiegelhalter et al. (2004) is proposed to analyze the primary outcome. An a priori distribution for the difference in this percentage of patients in remission after 6 months between both groups has been estimated from the elicitation of 15 clinician's opinions. A structured questionnaire similar to the one used in Parmar, Spiegelhalter, Freedman, and Chart Steering Committee (1994) was used and a short video explaining the study, the Bayesian design and why a priori opinions of clinicians are required were send to the clinicians along with the questionnaires. According to the literature (Spiegelhalter et al., 2004, p. 141), clinicians were as numerous as possible. They were child and adolescent psychiatrists with at least five patients corresponding to the patients included in this study. This group was a mixture of clinicians who had never and who had already referred a patient to TCP. Voluntarily, these clinicians were not experts in TCP to reduce allegiance bias as possible, that is, they have not published on the topic, they were not specialized in TCP, and have not participated regularly (i.e., at least 1 or 2 weeks) to TCP sessions. They were recruited among first‐line care teams who have already referred patients to TCP. A pessimistic a priori distribution was obtained from the experimental a priori distribution, dividing the mean of efficacy by 2 (keeping the same variance).

The final decision concerning treatment effect will be made from the observation of the posterior distribution of the log odds ratio (mixture of two normal distributions weighted by the variances: observed data and a priori distribution), the pessimistic posterior distribution (mixture of observed data and pessimistic a priori distribution), and from the distribution of observed data (uninformative prior). The 95% credible interval of efficacy will be estimated in these three situations.

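### The printed 80% power at 63 per group is not the operating characteristic of any of the three analyses that decide the primary result; the 40 real patients per group alone give about 60%.

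*Protocol article*

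**What the plan says.** Section 2.6 of the protocol article fixes the size: "Eighty participants will be enrolled in the study: 40 in experimental group and 40 in control group". Allocation is equal (2.3 Randomization: "Participants are randomized with a 1:1 allocation ratio").

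The same section derives a prior from expert opinion: "The mean (±SD) of this distribution is 0.195 (±0.0825) and corresponds an a priori of 23 “virtual” subjects per group". Adding those to the 40 real patients, "the a posteriori overall sample size will therefore be 63 subjects per group". It concludes that "a sample size of 63 per group would be sufficient to show a significant 23% difference in efficacy between groups" ("power = 80%, *α* = 0.05"). It presents the calculation as informational and as a frequentist equivalent, and closes by preferring the Bayesian design partly because fewer patients are needed.

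Section 3.1.1 (Primary objective) rests the final decision on three distributions. One is the posterior under the elicited prior. The second is the posterior under a pessimistic prior, obtained by "dividing the mean of efficacy by 2 (keeping the same variance" unchanged. The third is the data alone: "and from the distribution of observed data (uninformative prior" in the section's own label. A 95% credible interval is to be reported for each. The section names the log odds ratio as the scale and gives no rule for combining the three results.

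**The concern.** The only power figure in the article counts 23 subjects per group who will not be enrolled. The data-only analysis has no virtual subjects by definition, so it has 40 per group. The pessimistic analysis borrows from a prior centred at half the elicited effect. The elicited-prior analysis does borrow the prior, but treating it as 23 more patients per arm in a frequentist test is not the same as computing its posterior.

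The figure supports a claim of equivalence to a frequentist design and, with it, the case for enrolling fewer patients. The analysis closest to a frequentist one is the data-only analysis, and it falls well short of 80%. If TCP truly adds 23 points, the three intervals will often disagree by design. A reader who has been told 80% could then take an inconclusive data-only interval as evidence against efficacy.

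**Working it through.** **Inputs.** From 2.6: 40 real patients per group; elicited prior on the difference with mean 0.195 and SD 0.0825; 23 virtual subjects; 63 in total; 23 points; 80%; α = 0.05. From 3.1.1: pessimistic prior with half the mean and the same variance, so 0.0975 and 0.0825 on the difference scale.

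**Assumptions, none stated in the plan.** The test is two-sided; the control remission rate is as given below; success means that the lower 95% limit lies above no effect.

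**1. The plan's own figures.** Interval midpoints of the 20 elicited opinions give mean 0.195 and SD 0.0826. Then 0.195 × 0.805 / 0.0825² = 23.06, so 23. For 20% versus 43% and n = 63, the standard error is √(2 × 0.315 × 0.685 / 63) = 0.0828 under the null and √((0.16 + 0.2451)/63) = 0.0802 under the alternative. Power = Φ((0.23 − 1.96 × 0.0828)/0.0802) = 80.1%. The mirror case, 57% versus 80%, gives the same. The printed figure reproduces.

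**2. Data only, 40 per group, 20% versus 43%.**
- Pooled test: Φ((0.23 − 1.96 × 0.1039)/0.1006) = 60.4%.
- Unpooled test: Φ(0.23/0.1006 − 1.96) = 62.8%.
- Log odds ratio: effect 1.104, standard error 0.508, so Φ(2.173 − 1.96) = 58.4%; exact binomial enumeration gives 58.8%.

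Over control rates of 10% to 60% the range is about 54–74%. For 80% power with 40 per group at 20% control, the difference would have to be about 29 points.

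**3. Pessimistic prior, difference scale, normal updating.** The data precision is 1/0.1006² = 98.7 and the prior precision is 1/0.0825² = 146.9. The interval excludes zero when the observed difference exceeds (1.96 × √245.7 − 146.9 × 0.0975)/98.7 = 0.166. Power = Φ((0.23 − 0.166)/0.1006) = 73.7%. Over control rates of 10% to 57% it is about 65–85%.

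On the log odds ratio scale the plan gives no way to convert the prior. I halved the mean before or after conversion, and converted the SD by several reasonable routes, including giving the prior the weight of 23 subjects per group. The result is about 60–83% at 20% control and 57–70% at 57% control.

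**4. Elicited prior, difference scale.** The threshold becomes (1.96 × √245.7 − 146.9 × 0.195)/98.7 = 0.021, and power = Φ((0.23 − 0.021)/0.1006) = 98.1%. It is this high because the prior alone lies 0.195/0.0825 = 2.36 SDs above zero. Its precision also equals that of 146.9/98.7 × 40 ≈ 60 real patients per group at these rates, not 23.

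| Analysis (40 per group, 20% vs 43%) | Probability that the 95% interval is above no effect |
|---|---|
| Data only | 59–63% |
| Pessimistic prior, difference scale | about 74% |
| Elicited prior, difference scale | about 98% |
| Printed in 2.6 (63 vs 63) | 80% |

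**5. At the elicited mean of 19.5 points, 20% control.** Data only 46–50%; pessimistic about 62–63% on the difference scale; elicited about 96%.

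**The case against.** The strongest reply is that 2.6 limits its own claim. It says that a Bayesian sample size needs no formal justification, offers the calculation for information, frames it as a frequentist statement about 63 per group, and shows openly that 23 of the 63 are virtual. It nowhere says that the 80% holds for the data-only or pessimistic analysis. Section 3.1.1 sets no success threshold, so any probability of success needs a criterion supplied from outside. Operating characteristics by prior could also sit in a full protocol or analysis plan that is not shown.

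Much of this stands. The success criterion and the control rate are assumptions and are labelled as such. The informational label makes this an overstated reassurance and not a calculation error. It does not remove the point: the article prints a power figure, uses it to argue equivalence and a smaller trial, and then names deciding analyses that the figure does not describe. Correcting a printed figure is different from asking for omitted detail.

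Four stronger readings are tempting, and the document does not support them.
- **A reader might infer that the 80% is correct for the elicited-prior posterior and wrong only for the other two.** With the SD as printed, that posterior gives about 98%. It would give about 80–83% only if the prior carried the weight of 23 subjects per group.
- **A reader might apply the plan's conversion to the pessimistic mean and conclude that this prior is worth fewer virtual subjects.** Section 3.1.1 keeps the variance, and in normal updating equal variance means equal weight. Only the centre moves.
- **A reader might quote a narrow range for the pessimistic analysis.** Without a stated conversion to the log odds ratio, the plan does not support one.
- **A reader might conclude that more patients are required.** The plan sets no power target for the data-only analysis, so this does not follow.

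**Conclusion.** The point holds as wrong as written: the stated power is not delivered by the design, although the arithmetic behind it reproduces. The firmest part is the data-only result, which is about 60% at the control rates that reproduce the 80% and below 80% at every rate from 10% to 60%. The pessimistic result falls below 80% at most control rates on the difference scale, but can exceed it near 10% control or under some log odds ratio conversions. The elicited result is far above 80%: about 98% on the difference scale, and from about 93% to above 99% on the log odds ratio scale. All of these figures rest on the assumed control rate, on the 95% interval lying above no effect as the criterion, and on normal updating with the printed prior. The remedy is a correction to the reported design properties; the sample size and the planned analyses do not change.

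**What to change.** In 2.6, replace the single statement of 80% at 63 per group with the probability that the 95% credible interval excludes no effect, at 40 per group, separately for each of the three analyses in 3.1.1. Give it at 23 and at 19.5 points over a stated range of control remission rates. State as assumptions the success criterion, the scale, and how each prior is converted to the log odds ratio. If the 80% is kept for reference, say that it is a frequentist 63-versus-63 figure that applies to none of the three analyses, and that the 40 real patients per group alone give about 60%. Keep 80 patients.

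The cost is a short calculation and a reworded paragraph. The downside is a less favourable printed power for the data-only analysis and, at most control rates, for the pessimistic one.

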### Data management

2.7

In each center, the investigator or a collaborator will collect the data based on patient's medical file, interrogation on the cultural context and history of migration and questionnaires filled at each collection time (Appendix S4). All the data will be entered electronically via a web browser recorded in a e‐CRF (Cleanweb, Télémédecine). The access to the final trial dataset will be restricted to all the persons authorized by the sponsor in agreement with the scientific committee. This research is governed by the CNIL “Reference Method for processing personal data for clinical studies” (MR‐001). There will be no data monitoring committee.

### Specific committees for the study

2.8

A steering committee and a scientific committee will be composed of at least the coordinating investigator, the methodologist, the scientific director (for the scientific committee), and the sponsor's appointed representatives for the study. They will meet once a year to define the overall organization of the study, coordinate the information, monitor the research process, suggest procedures to be followed during the study, recommend changes to the protocol during the study if necessary. Every important protocol modification will be amended on clinicaltrial.gov and submitted to CPP for approval.

No particular risk of any adverse event has been identified that could be caused by a psychotherapy properly conducted, however adverse events will be collected and described in the study report and any serious adverse event will be reported to the sponsor regardless of causality.

## RESULTS

3

### Quantitative analysis

3.1

Analyses will be performed according to the intention to treat (ITT) principle and no interim analysis will be performed. For the primary objective, as the iCGI severity score ≥4 is an inclusion criterion, all patients will have at least a measure at W0 and will be included in the ITT analysis. For patients with missing data on the iCGI assessment at W34, in case of less than 5% of missing data, the last observation carried forward will be used as imputation method, multiple imputations will be used otherwise (Jakobsen, Gluud, Wetterslev, & Winkel, 2017). For the secondary objectives, as mixed models will be used, missing data will not be imputed. For every objective, per protocol analyses will be performed as sensitivity analyses. The per protocol population is defined as patients for who the baseline and the last planned measure (W34) of the considered endpoint are available and who received the allocated intervention assigned by the randomization.

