This measure consists in a filmed semi‐structured clinical interview conducted by a psychologist trained in transcultural care, in the presence of an interpreter speaking the native language of the family. The interview guide has been constructed by specialists of transcultural care in childhood and adolescence (Appendix S2). It explores the severity of the symptoms in the past few weeks with the patient and the family. After the end of the follow‐up of the last included participant, three blinded independent experts will watch the film and rate the patient on a 7‐level scale: 1—normal, not at all ill; 2—borderline mentally ill; 3—mildly ill; 4—moderately ill; 5—markedly ill; 6—severely ill; and 7—among the most extremely ill patients. Remission is defined as a mean iCGI score over the 3 experts lower than 4.

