## DISCUSSION

4

In total, results will encourage the development and routinization of TCP for second‐line use and its adaption as a first‐line technique in this population. Today, the standard psychotherapeutic care offered for depression in children and adolescents does not lead to complete remission in patients with migration backgrounds, who present complex clinical depression with numerous comorbidities and requiring long care and substantial human and financial resources. This results in longer states of depression, which often become chronic. Morbidity is greater in the short, medium, and long term. In the short term, the risk of suicidal action rises, as do anxiety symptoms, repercussions on schooling (failures), and on social bonds (marginalization and violence). The consequences in adulthood on individual and social functioning and healthcare costs are large (Weissman et al., 1999). Every important trial result will be communicated to participants, healthcare professionals, and the public through publications, poster and oral communication in congress, and other media.

Benefits of the research for the patients will be faster improvement of depressive symptoms, directly affecting short‐ and long‐term morbidity. The benefits in terms of public health will also be important. The flow of migrant families and unaccompanied minors into France continues, coming from ever more distant geographic and cultural origins and often been exposed to complex traumatic situations. The numbers of descendants of migrants are increasing rapidly. The care offered to these children when they have resistant complex depression must include a cultural component (Georgiades, Paksarian, Rudolph, & Merikangas, 2018) to reduce both direct and indirect healthcare costs. The qualitative aspects will allow us to specify the therapeutic processes within this psychotherapy and make them more reproducible and transmissible: What are the principal therapeutic aspects in the visit? How can we extract them to make them more effective? Finally, the analysis of data about the acceptability of this psychotherapy will allow us to define the limits of its indications.

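### The rule for a missing W34 iCGI takes no account of why it is missing, so a patient who died, or could not be filmed after a suicidal act or admission, could count as in remission

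*Protocol article*

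**What the plan says.** Three statements in the protocol article fix how the primary endpoint is obtained.

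- Section 2.4.1 (Primary endpoint) defines success only through the rating of the filmed W34 interview: "Remission is defined as a mean iCGI score over the 3 experts lower than 4".
- Section 3.1 (Quantitative analysis) puts all patients in the intention-to-treat analysis, because entry already requires a baseline iCGI.
- The same section fills any missing W34 iCGI by a rule that depends only on how much is missing: "in case of less than 5% of missing data, the last observation carried forward will be used as imputation method, multiple imputations will be used" in all other cases.

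Other passages bear on how such gaps could arise. The Discussion says of depression that does not remit: "In the short term, the risk of suicidal action rises, as do anxiety symptoms". Section 2.3 says of usual care, in both arms: "It may include psychotherapy (individual, in group, or family therapy), medications, or institutional care", with inpatient stays among the examples. Table 2 lets visits 1 to 4 take place at the inclusion centre, the first-therapy centre or the family's home, but W34 only at the inclusion centre.

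**The concern.** Some reasons for a missing film are themselves information about the outcome. A patient who died is not in remission, and no imputed W34 score has a meaning for that patient. A patient who could not be interviewed because of a suicidal act or a psychiatric admission is hardly a treatment success either. The stated rule treats these patients like a family that missed an appointment. A rating of 3 at W27 followed by such an event gives remission under carrying forward. Under multiple imputation, the model borrows from patients who were well enough to be filmed.

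At stake is the content of the primary endpoint: a serious failure could enter as a success. With 40 patients per arm, a single case is visible in the result.

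**Working it through.** **Inputs.** 40 patients per arm, 80 in all (section 2.6); remission if the mean rating is below 4 (2.4.1); threshold of 5% missing (3.1); earlier iCGI assessments at W0, W6, W13, W20 and W27 (Table 2); baseline iCGI of at least 4 (2.1.1). The article gives no rate of death, suicidal acts or admission, so the counts below are assumptions.

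**The plan's own figures, for scale.** Section 2.6 states a prior mean and SD that "is 0.195 (±0.0825) and corresponds an a priori of 23" virtual subjects per group. Check: 0.195 × 0.805 / 0.0825² = 23.06, so 23, and 23 + 40 = 63. The claimed power for a 23-point difference with 63 per group is reproduced at 80.1% for 20% versus 43% (two-sided, no continuity correction). The 20% control rate is assumed, since the article gives none. The pessimistic prior in 3.1.1 halves the mean: 0.195 / 2 = 0.0975. Nothing in this point depends on these figures; they only show what 2.5 points should be compared with.

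**Step 1: which rule applies.** 3/80 = 3.75% is under 5%, so last observation carried forward applies. 4/80 = 5.0% is not under 5%, so multiple imputation applies. Carrying forward therefore concerns at most 3 patients, over both arms and all reasons.

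**Step 2: when an affected patient becomes a remission.**
- Carried forward, last rating 4 or more, or baseline only: not in remission.
- Carried forward, last rating below 4: in remission.
- Multiple imputation: in remission with some probability p that depends on the model. I assume p between 0.20 and 0.50.

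**Step 3: size per patient.** One patient is 1/40 = 2.5 percentage points of an arm. Carrying forward adds 0 or 2.5 points. Multiple imputation adds p × 2.5, that is 0.20 × 2.5 = 0.5 to 0.50 × 2.5 = 1.25 points on average.

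**Step 4: extremes.** Three carried-forward remissions in one arm: 3 × 2.5 = 7.5 points. Four affected patients under multiple imputation: 4 × 0.20 = 0.8 to 4 × 0.50 = 2.0 expected remissions, or 2.0 to 5.0 points if all are in one arm.

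**Step 5: illustration on the odds ratio.** Assume 17/40 versus 8/40 remissions and the uninformative prior, one of the three analyses in 3.1.1. OR = (17/23)/(8/32) = 2.96; SE of log OR = √(1/17 + 1/23 + 1/8 + 1/32) = 0.508; 95% interval 1.09 to 8.01. If imputed remissions in the experimental arm are recoded as non-remission:

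| Recoded | Difference (points) | OR (95% interval) |
|---|---|---|
| 0 | 22.5 | 2.96 (1.09 to 8.01) |
| 1 | 20.0 | 2.67 (0.98 to 7.25) |
| 2 | 17.5 | 2.40 (0.88 to 6.56) |
| 3 | 15.0 | 2.15 (0.78 to 5.92) |

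This is the adverse case, with every affected patient in one arm. The same misclassification in the control arm would shrink the observed difference instead.

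**The case against.** The strongest reply is that the article never says a death or an admission is to be handled as missing data. Special rules for such events are commonly left to the full protocol or SAP, and neither is shown. That limits the point but does not remove it. The article is not merely silent: it includes everyone, defines remission only by the film, and gives one rule for every absent W34 rating. Read literally, that rule covers these patients.

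Several further replies stand and set the size of the point.
- Section 2.1.1 excludes severe mental disorder that may hinder the therapy, with high suicidal risk in its example. This lowers the expected number of events, although it acts only at entry.
- Section 2.8 has adverse events collected and described and serious ones reported to the sponsor, so the events themselves stay visible.
- Inpatient care is allowed within usual care, so admission alone does not make W34 missing.
- The Discussion's remark on suicidal action is background, not an event rate for this trial.
- Carrying forward does not favour remission by default.

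A reader might infer more than the documents support. One inference is that the per-protocol analysis is also compromised because it needs a W34 measure. It is a sensitivity analysis only, and that is its declared definition. Another is that attendance at W34 must differ by arm because control families have no reason to come. Controls are on a waiting list for TCP (2.3) and may start it after W34 (2.5.4), so they do have a reason. A third is to take 7.5 points as the likely effect. That needs all three carried-forward patients to have had a serious event, in the same arm, each with a last rating below 4.

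**Conclusion.** The point holds in limited form. As written, section 3.1 lets a patient who died, or whose W34 interview was prevented by a suicidal act or psychiatric admission, be counted as in remission. Under carrying forward this happens only if the last rating was below 4; under multiple imputation it happens with some positive probability. Each such patient moves one arm's rate by at most 2.5 points: upwards for TCP if in the experimental arm, against it if in the control arm. If events are balanced between arms, much of the error in the difference cancels.

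The number of events is unknown and probably small, so a large bias is not shown. The change is worth making because the correct classification is close to definitional and costs little. The conclusion assumes that the full protocol and SAP contain no separate rule; if they do, only the article's wording needs aligning.

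**What to change.** 1. In section 2.4.1, state that death before W34, or a W34 interview not done because of a documented suicidal act or psychiatric admission, counts as not in remission.
2. Record the reason for every missing W34 film, and have it classified by someone unaware of the arm, since deciding that an event caused the absence is a judgement.
3. In section 3.1, limit last observation carried forward and multiple imputation to films missing for other reasons.
4. In Table 2, allow W34 filming at the first-therapy centre or the family's home as a fallback when the patient cannot travel, as visits 1 to 4 already allow.

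The cost is a sentence or two in each section, one data field and one table entry. There are small downsides: a slightly lower remission rate, the work of blinded classification, and a few films in a different setting, which could hint at the arm to the expert raters.
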